### Allocation and randomization

All participants who met the study inclusion and exclusion criteria are randomly assigned in a 1:1 ratio to the tourniquet and non-tourniquet groups by the method of random envelope. Prior to study initiation, an independent statistician will use the SAS 9.4 software (SAS Inc., Cary, NC, USA) to generate a blocked random number sequence in permuted blocks of 4 participants. The electronic data capture system automatically generates participant ID numbers in sequence, which are subsequently linked to tourniquet assignments at randomization. Both the participants’ ID numbers and their allocation groups (tourniquet or non-tourniquet) will then be sealed in an envelope. The scientific secretory of this trial is responsible for enrolling participants and assigning participants to intervention (Table 1).

**Table 1 Tab1:** Schedule of enrollment, interventions, and assessments

Time point		Study period									
		Enrollment	Allocation	Post-allocation							
				t1	t2	t3	t4	t5	t6	t7	t8
Enrollment	Eligibility screen	X									
	Informed consent	X									
	Randomization		X								
Interventions	Tourniquet group				X						
	Non-tourniquet group				X						
Assessments	Demographic data			X							
	Quadriceps thickness			X			X				
	Quadriceps stiffness			X			X				
	Isokinetic muscle strength test								X		
	3D gait analysis								X		
	Posture stability testing								X		
	Thigh circumference			X		X	X				
	VAS score					X	X	X	X		
	Opioid consumption						X				
	Knee function score			X						X	X
	Postoperative satisfaction score									X	X
	Operation time				X						
	Intraoperative blood loss				X						
	Perioperative blood loss						X				
	Blood transfusion rate					X	X	X			
	d-dimer			X		X	X				
	C-reactive protein			X		X	X				
	Complications					X	X	X	X	X	X

*t1* before the operation, *t2* in operation, *t3* 1 day after the operation, *t4* 3 days after the operation, *t5* 2 weeks after the operation, *t6* 6 weeks after the operation, *t7* 3 months after the operation, *t8* 1 year after the operation

Participants and researchers who offer ultrasound and rehabilitation evaluation will all be blinded to the group allocation. However, in case of any medical emergency in the study period, allocation will be unblinded to researchers and clinicians for further medical treatment.

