### Outcomes and measures

#### Preoperative measurements

Demographic information of all the patients is collected, including gender, age, height, weight, and BMI. Baseline outcomes including quadriceps thickness and stiffness, thigh circumference, knee function scores, hematocrit and hemoglobin level, d-dimer, and C-reactive protein level in the serum are evaluated before surgery but after randomization and allocation.

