#### Primary outcome

Bilateral lower extremity ultrasonography is performed before and 3 days after surgery to evaluate the thickness of the quadriceps muscle. The inspection is performed by a Canon Apilio I900 ultrasound with L18-5 probe. The probe is placed vertically on the body surface without compressing. The maximum distance from the front to the back of the quadriceps on the horizontal cross-section is selected as the quadriceps thickness; meanwhile, muscle echo and texture are observed. The ultrasound measurements are conducted by the same ultrasound examiner.

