### Statistical analysis

The statistician who conducted the analysis is blinded to the group allocation. Summary statistics are used to describe the participant characteristics of the trial groups at baseline in the intention-to-treat (ITT) analysis set. The missing data of quadriceps thickness and stiffness is imputed by the multiple imputation method. The results of multiple imputation data are used as a type of sensitivity analysis for comparing primary outcomes between the groups.

For primary outcomes comparison, the ITT analysis is performed to evaluate the differences between the groups, and effective analysis population (EAP) and per-protocol (PP) analyses are also performed for sensitivity assessment. The primary outcomes do not follow the Gaussian distribution and are presented as median (IQR) and tested by the Mann-Whitney *U* test. Bonferroni correction is used to reduce the significance level. The means (95% CIs) of the between-group differences of the medians are calculated by the bootstrap method (1000 replications). The generalized linear mixed models (GLMM) are also performed for the primary endpoint, including group, gender, age, height, and weight as fixed covariates.

For comparing the secondary and exploratory endpoints, continuous data are presented as means (SDs) or medians (IQRs) as appropriate. The secondary endpoints are analyzed by the linear mixed model (LMM), adjusted for gender, age, height, weight, and other covariates. The correlation type of different measurement time points is assumed as the first-order autocorrelation in the LMM. Exploratory endpoints are compared by the Mann-Whitney *U* test, and the significance level is submitted to Bonferroni correction.

For safety endpoints, categorical data are presented as counts and percentages and tested by the Pearson’s chi-square test or Fisher’s exact test. The 95% CIs of absolute risk differences between the groups are calculated by the Newcombe-Wilson Score method. All statistical analyses are conducted with the statistical package SPSS, V.18.0 (SPSS Inc.) and the R 3.4.0 software. Besides Bonferroni correction, statistical significance is defined as *p* < 0.05with two-sided testing.

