### Sample size estimation

The primary hypothesis of this trial based on our previous pilot study is that quadriceps thickness in the tourniquet group is not less than that in the non-tourniquet group. The risk of class I error of the hypothesis is controlled within 5% during sample size estimation (*α* = 0.05).

Quadriceps thickness is 3.1 ± 0.5 cm in the non-tourniquet group and 3.1 ± 0.6 cm in the tourniquet group. Non-inferiority margin (*σ*) is 0.31, which is 10% of the average quadriceps thickness in the non-tourniquet group, *α* = 0.025 (unilateral), *β* = 0.2. We apply the non-inferiority test by PASS14 and find that we need at least 51 participants in each group. We determine that a total of 51 participants per group would have an 80% statistical power in detecting a tourniquet impact between the two groups. This will result in a total of 102 participants. Estimating that 30% of participants would drop out, a sample size of 130 participants is considered to be adequate for this study.

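### No listed primary analysis adjusts for the preoperative quadriceps thickness that the trial already collects under blinding, at an avoidable cost in precision

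*Protocol article*

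**What the plan says.** All references are to the protocol article.

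- **Measurement (Primary outcome; Table 1).** "Bilateral lower extremity ultrasonography is performed before and 3 days after surgery to evaluate the thickness of the quadriceps muscle", by one examiner. Table 1 places thickness at t1 (before surgery) and t4 (day 3) only.
- **Baseline status (Preoperative measurements).** "Baseline outcomes including quadriceps thickness and stiffness, thigh circumference, knee function scores" and others "are evaluated before surgery but after randomization and allocation".
- **Blinding (Allocation and randomization).** "Participants and researchers who offer ultrasound and rehabilitation evaluation will all be blinded to the group allocation".
- **Primary test (Statistical analysis).** "The primary outcomes do not follow the Gaussian distribution and are presented as median (IQR) and tested by the Mann-Whitney" U test. The accompanying interval is a bootstrap interval, with 1000 replications, for the between-group difference of medians.
- **Additional model for the primary endpoint (Statistical analysis).** A generalized linear mixed model (GLMM), "including group, gender, age, height, and weight as fixed covariates".
- **Hypothesis and size (Study design; Sample size estimation).** Non-inferiority is stated for thickness itself. The inputs are 3.1 ± 0.5 cm without and 3.1 ± 0.6 cm with a tourniquet. The margin is 0.31 cm, described as "10% of the average quadriceps thickness in the non-tourniquet group", with one-sided alpha 0.025, 80% power and 51 per group.

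**The concern.** The non-inferiority answer depends on how wide the between-group interval is against a margin of 0.31 cm. Muscle thickness varies between patients for reasons unrelated to the tourniquet, and the preoperative scan of the same leg is the most direct measure of that variation the trial collects. The rank test and the median interval take no covariate, and the GLMM's list of covariates does not include the scan. As listed, no primary analysis uses it as an adjustment variable.

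At stake is efficiency. A wider interval makes it more likely that a tourniquet that is truly non-inferior fails to be shown so, with data already in hand that could narrow the interval. This is a matter of choices the article makes. It names the test, the interval method, the replication count and the model covariates. For secondary endpoints it leaves the covariate list open, but for the primary endpoint it does not.

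**Working it through.** **Inputs from Sample size estimation.** SDs 0.5 and 0.6 cm, true difference 0, margin 0.31 cm, one-sided alpha 0.025, power 0.80, 1:1 allocation.

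**Assumed, not in the article.** The correlation r between preoperative and day-3 thickness of the same leg, taken from 0.3 to 0.8 and as common to both arms.

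**Step 1: reproduce the plan's figure.**
- Root-mean-square SD = √[(0.5² + 0.6²)/2] = √0.305 = 0.552 cm.
- Normal approximation: n = 2 × (1.960 + 0.842)² × 0.305 / 0.31² = 49.8, so 50 per arm.
- With the t distribution, 50 per arm gives power 0.794 and 51 gives 0.802 (Welch 0.801).

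The stated 51 is therefore reproduced from the raw SDs with no pre/post correlation. The trial is sized for an unadjusted comparison of thickness levels in means.

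**Step 2: unadjusted precision at 51 per arm.**
- SE = 0.552 × √(2/51) = 0.109 cm.
- 95% half-width = 1.984 × 0.109 = 0.217 cm.

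**Step 3: adjust for preoperative thickness.** The residual SD is 0.552 × √(1 − r²), with one fewer degree of freedom. For r = 0.5 the SE is 0.109 × 0.866 = 0.095 cm and the half-width is 1.984 × 0.095 = 0.188 cm. Power is from the noncentral t distribution with noncentrality 0.31/SE.

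| Assumed r | Half-width at 51 per arm (cm) | Power at 51 per arm | n per arm for 80% power |
|---|---|---|---|
| unadjusted | 0.217 | 0.80 | 51 |
| 0.3 | 0.207 | 0.84 | 47 |
| 0.5 | 0.188 | 0.90 | 39 |
| 0.7 | 0.155 | 0.98 | 27 |
| 0.8 | 0.130 | 0.997 | 19 |

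**Step 4: what if change from baseline was meant?** With equal SDs at both times, the SD of a change score is 0.552 × √[2(1 − r)]. At 51 per arm the half-width is 0.257 cm (r = 0.3), 0.217 (0.5), 0.168 (0.7) and 0.137 (0.8). A plain change score is worse than no adjustment below r = 0.5, equal to it at 0.5, and still wider than the adjusted analysis at every r shown. So the analysed variable matters, and adjustment is the better choice under either reading.

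**Step 5: where chance baseline imbalance enters.** If preoperative SDs are like the planning SDs, the chance difference in starting thickness has SE 0.109 cm. The unadjusted variance splits into a part r² × 0.109² carried by that imbalance and a part (1 − r²) × 0.109² that remains. The imbalance is thus already inside the 0.217 cm. Adjustment removes that part, and it must not be counted again as a separate harm.

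**Limit of these figures.** They describe a difference in means, the scale of the sample-size section. The planned rank test and bootstrap median interval were not themselves evaluated.

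**The case against.** **The analysed variable is not stated.** A reader might infer that only the day-3 value is analysed and that the preoperative scan goes unused. No sentence says so. The primary outcome is defined with both scans, and the Statistical analysis section names no time point, level or change. The hypothesis and raw SDs point to the level but do not settle it. A mixed model could also hold the preoperative scan as a repeated response, though no time term is listed. This objection stands. What remains is that the scan is not an adjustment variable in anything listed.

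**The GLMM removes part of leg size.** It does, through gender, height and weight. The gain over that model would be smaller than the table shows, by an amount the article does not allow one to compute. The rank test and median interval get no such help.

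**An unadjusted randomised comparison is valid.** Correct. A reader might infer bias, or a raised risk of a false non-inferiority claim. The document supports neither, and the plan's 80% power was set without adjustment.

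**The gain depends on an unknown correlation.** Correct. At r = 0.3 it is slight. Day 3 is a time when the trial also measures postoperative swelling, so a high r cannot be presumed.

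**The baseline is taken after randomisation.** This does not disqualify it. It precedes surgery, and the patient and the ultrasound examiner are blinded.

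**Non-normality favours a rank test.** A robust or bootstrap interval allows for non-normality in an adjusted model.

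**The effect measure changes.** It does, from a difference of medians to an adjusted mean difference. That is a real cost, though the means and the margin in the sample-size section are already on the mean scale.

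**Conclusion.** The point holds as one of efficiency. Preoperative thickness of the operated leg is collected under blinding and is not an adjustment variable in the primary test, the primary interval or the listed covariates of the GLMM. The article also leaves open whether day-3 thickness or change is compared.

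On the mean-difference scale at 51 per arm, adjustment would narrow the half-width from 0.217 cm to between 0.207 and 0.130 cm. Power would rise from 0.80 to between about 0.84 and above 0.99, for r from 0.3 to 0.8. This rests on the plan's SDs, a true difference of zero and an assumed correlation.

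The same argument might seem to extend to the secondary endpoints. It does not, because their covariate list is open and completing it is routine detail.

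**What to change.** In Statistical analysis, state that the primary non-inferiority estimate is the between-group difference (tourniquet minus non-tourniquet) in day-3 thickness of the operated leg. Take it from a linear model with group, preoperative thickness of the same leg, gender, age, height and weight. Give a heteroscedasticity-robust or bootstrap 95% CI and compare its lower limit with -0.31 cm. Keep the Mann-Whitney test and the medians as supporting analyses.

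This needs no new data, visits or patients. The cost is the change of effect measure, from a difference of medians to an adjusted mean difference. With 84 participants already recruited and no interim analysis planned, it should be recorded as a protocol amendment before any unblinded analysis.

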**Fig. 1 Fig1:**
[figure not shown]
Flowchart of the study process

We assume the primary hypothesis of this trial is that quadriceps thickness in the tourniquet group is not less than that in the non-tourniquet group (non-inferiority study).

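### 1000 bootstrap replications leave avoidable seed noise in the primary-outcome interval; if its lower limit is read against the 0.31 cm margin, about 3–4% of trials could flip

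*Protocol article*

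**What the plan says.** The study design section states the primary hypothesis as "quadriceps thickness in the tourniquet group is not less than that in the non-tourniquet group (non-inferiority study"). The sample size section supplies the inputs. It assumes a mean of 3.1 cm in both arms, with an SD of 0.5 cm without and 0.6 cm with a tourniquet. On the margin it says: "Non-inferiority margin (*σ*) is 0.31, which is 10% of the average quadriceps thickness in the non-tourniquet group". The calculation there is one-sided at 0.025 and aims for 80% power.

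The Statistical analysis section handles the same outcome in three ways:

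- **Test.** The primary outcomes "are presented as median (IQR) and tested by the Mann-Whitney *U* test", and in general "statistical significance is defined as *p* < 0.05with two-sided testing".
- **Estimate.** "The means (95% CIs) of the between-group differences of the medians are calculated by the bootstrap method (1000 replications").
- **Model, listed as a further analysis of the same endpoint.** "The generalized linear mixed models (GLMM) are also performed for the primary endpoint, including group, gender, age, height, and weight as fixed covariates".

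The 0.31 cm margin appears only in the sample size section. The analysis section does not name the type of bootstrap interval and does not say which quantity is set against the margin.

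**The concern.** A one-sided 0.025 non-inferiority test corresponds to checking whether the lower limit of a two-sided 95% interval lies above −0.31 cm. The Mann-Whitney test as described contains no margin, and no interval is described for the mixed model. The bootstrap interval is therefore the natural candidate for that comparison.

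With 1000 replications, a percentile lower limit is read at about the 25th smallest of 1000 resampled differences. A quantile that far into the tail moves visibly from one run to the next. The movement matters only when the limit falls close to a fixed threshold, and under the plan's own inputs it is expected to fall close. If the interval is used for the decision, a conclusion on the primary hypothesis could in a few trials in a hundred depend on the random seed and not on the data. The article itself states the figure of 1000, so this concerns a number the document fixes and not a detail it leaves out.

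**Working it through.** **Inputs.** From the sample size section: SD 0.5 cm (non-tourniquet) and 0.6 cm (tourniquet), both means 3.1 cm, margin 0.31 cm, one-sided α 0.025, power 80%, 51 evaluable per arm. From the study design section: 65 randomised per arm. With the stated 30% dropout, 65 × 0.7 = 45.5 per arm remain, so 45 or 46 is the low end. From the analysis section: 1000 replications and a 95% interval for the difference in medians. Assumptions added here: the lower limit is compared with −0.31 cm, and a percentile interval is used unless stated otherwise.

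**1. The plan's own figure.** The average variance is (0.25 + 0.36)/2 = 0.305. The normal approximation gives n = 2 × (1.960 + 0.842)² × 0.305 / 0.31² ≈ 49.8, so 50 per arm. Power from the noncentral t distribution is 0.793–0.794 at 50 and 0.801–0.802 at 51. The plan's 51 is reproduced.

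**2. Sampling error of the median difference.** SE = √(π/2) × √(0.61/n).

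- 51 per arm: 1.2533 × 0.1094 = 0.137 cm
- 65 per arm: 1.2533 × 0.0969 = 0.121 cm

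With no true difference, the expected lower limit at 51 per arm is −1.96 × 0.137 = −0.269 cm. That is about 0.04 cm from the margin.

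**3. Bootstrap noise in the limit.** For B replications, the SD of an estimated 2.5% quantile in SE units is √(0.025 × 0.975/B)/φ(1.96). With B = 1000 this is 0.00494/0.0584 = 0.0845. In cm it is 0.0116 at 51 per arm and 0.0103 at 65. Direct simulation gives slightly more: 0.0135 at 46, 0.0129 at 51 and 0.0114 at 65 per arm.

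**4. How often two seeds disagree.** To a close approximation, this is the density of the limit at −0.31 times the mean absolute gap between two runs. At 51 per arm:

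- z = (−0.31 + 0.269)/0.137 ≈ −0.30, so the density is 0.381/0.137 ≈ 2.78 per cm
- mean gap = 0.0116 × √2 × 0.798 ≈ 0.0131 cm
- product ≈ 0.036, about 1 in 28

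The same calculation at 65 per arm gives about 0.032.

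**5. Simulation of the percentile limit** (12,000 trials per row, two independent bootstraps each, no true difference, B = 1000):

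| Per arm | Normal data | Lognormal data |
|---|---|---|
| 45 | 3.9% | 4.0% |
| 51 | 3.8% | 4.0% |
| 65 | 3.5% | 3.3% |

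The median shift of the limit between seeds is about 0.01 cm. Its 95th percentile is about 0.03–0.04 cm.

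**6. Sensitivity to what the article does not fix** (B = 1000):

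| Scenario | Two seeds disagree |
|---|---|
| Basic interval, 51 per arm, no difference | 1 in 33 to 35 |
| Normal-type interval, 51 per arm, no difference | 1 in 38 to 41 |
| Percentile, 51 per arm, true difference −0.10 cm | about 1 in 28 |
| Percentile, 51 per arm, true difference −0.155 cm | about 1 in 37 |
| Percentile, 51 per arm, true difference +0.10 cm | about 1 in 42 |
| True difference at the margin, −0.31 cm | about 1 in 200 |

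The −0.155 row is from the normal-theory calculation. The margin row spans 1 in 179 (theory, 51 per arm) to 1 in 218 (simulation, 65 per arm).

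**7. With 10,000 replications.** Noise shrinks by √10 = 3.16, so the rate at 51 per arm should be about 3.6%/3.16 ≈ 1.1%. Simulation of 5,000 trials gives 1.4%, about 1 in 74.

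**The case against.** The strongest reply is that the decision at issue is not in the document. The stated test is a two-sided Mann-Whitney test, and the bootstrap interval is listed beside it as an estimate. No sentence says its lower limit is held against −0.31 cm. A reader might infer that two analysts following the plan to the letter could reach opposite non-inferiority conclusions. The article does not support that, because it sets out no such rule to follow. This part of the reply stands, and the flip rate must be stated as conditional. How the margin enters the analysis is a separate and larger question, which a change in replications does not answer.

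A reader might also infer that this interval is the only quantity that could be compared with the margin. That goes too far. The mixed model includes group as a fixed effect, and its estimate would ordinarily carry an interval in cm that is free of bootstrap noise.

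Third, a single figure such as 1 in 28 should not be quoted without its conditions. It belongs to a percentile interval, no true difference and roughly 51–65 per arm. Where a false claim of non-inferiority is the main worry, with the truth at the margin, the rate is near 1 in 200.

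Fourth, the noise is small next to sampling error. At 51 per arm, 0.0129/0.137 is about 9% of the SE, which adds less than 1% to the variance (0.094² ≈ 0.009). A flip needs a limit already within a few hundredths of a centimetre of the margin. This is correct, and it keeps the point minor.

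What survives is narrow. The article states a number, a larger one is better for a tail limit, and any bootstrap limit later tied to the margin would inherit the noise.

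**Conclusion.** The point holds as a minor refinement. It is neither an error nor a contradiction in the plan. If the lower 95% percentile limit of the bootstrap interval is compared with −0.31 cm, with SDs of 0.5 and 0.6 cm and no true difference, two seeds would disagree on non-inferiority in about 3–4% of trials at 51–65 per arm. Other interval types and most other true differences lower that rate.

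The result rests on three assumptions from outside the document: that this interval carries the decision, the interval type, and the true difference. It does not depend on normal data, since lognormal data give similar rates. If the decision is taken from the model's group effect instead, the flip rate does not apply and only the reproducibility of a descriptive interval remains.

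**What to change.** In the Statistical analysis section, change the number of bootstrap replications from 1000 to at least 10,000, and state that a fixed seed is set in advance and recorded with the code. The two parts do different work. More replications make the limit more accurate and cut two-seed disagreement to roughly 1–1.5% under the assumptions above. The seed makes the run reproducible but no more accurate. The same wording serves any other bootstrap interval that is later chosen for the comparison with the margin.

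The cost is one number and one clause of text, plus seconds of computing. Sample size, visits, measurements and patients are unaffected.

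### Preoperative quadriceps thickness is collected but used neither in the primary test nor in the primary model's covariate list, so the non-inferiority comparison forgoes precision and leaves chance baseline imbalance unadjusted

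*Protocol article*

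**What the plan says.** **Measurement.** The Primary outcome section states: "Bilateral lower extremity ultrasonography is performed before and 3 days after surgery to evaluate the thickness of the quadriceps muscle". One examiner does all the scans. Table 1 places thickness at t1 (before the operation) and t4 (day 3). The Preoperative measurements section counts thickness among the baseline outcomes, which "are evaluated before surgery but after randomization and allocation". Patients and ultrasound evaluators are blinded (Allocation and randomization).

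**Hypothesis.** The Study design section sets it on thickness itself: "quadriceps thickness in the tourniquet group is not less than that in the non-tourniquet group (non-inferiority study"). The Sample size estimation section uses the same scale: "Quadriceps thickness is 3.1 ± 0.5 cm in the non-tourniquet group and 3.1 ± 0.6 cm in the tourniquet group", with a margin of 0.31 cm. Change from baseline is not mentioned.

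**Analysis.** Under Statistical analysis, the primary outcomes "are presented as median (IQR) and tested by the Mann-Whitney" U test. The effect measure is the mean with 95% CI "of the between-group differences of the medians are calculated by the bootstrap method (1000 replications"). A generalized linear mixed model (GLMM) is also fitted for the primary endpoint, "including group, gender, age, height, and weight as fixed covariates". Preoperative thickness appears in none of the three. The model for secondary endpoints is worded differently: "adjusted for gender, age, height, weight, and other covariates".

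**The concern.** Between-patient spread is large against the margin. SDs of 0.5 and 0.6 cm are 16% and 19% of the 3.1 cm mean, and the margin is 10% of it. For a continuous outcome, the same measurement taken before the intervention is usually the strongest available predictor. Here it comes from the same muscle, scanned by the same blinded examiner a few days earlier. The plan adjusts for general body-size variables and leaves this one out.

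Two things are at stake:

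- **Precision.** A non-inferiority conclusion depends on where the lower confidence limit falls. An interval wider than necessary can leave a truly non-inferior result unproven.
- **Chance imbalance.** If one arm happens to start with thicker muscle, an unadjusted day-3 comparison carries part of that head start into the result.

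This is more than detail left to an analysis plan. The article states the primary test and a closed covariate list for the primary model, and the outcome's own baseline is absent from both.

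**Working it through.** **Inputs.** SDs of 0.5 and 0.6 cm, true difference 0, margin 0.31 cm, one-sided alpha 0.025, 51 per group, 130 in total and 30% dropout all come from Sample size estimation. Two further inputs are assumptions: the correlation r between preoperative and day-3 thickness, shown as a range, and equal variance at the two times.

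**1. The plan's own figure.** SE = sqrt((0.25 + 0.36)/n). At n = 51 this is sqrt(0.61/51) = 0.1094 cm, so 0.31/0.1094 = 2.83. The noncentral t with 100 df gives power 0.802, and n = 50 gives 0.794. The stated 51 per group is therefore reproduced from unadjusted SDs, with no credit taken for baseline.

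**2. With baseline adjustment.** In an ANCOVA the residual variance is multiplied by (1 - r²), so SE = sqrt(0.61(1 - r²)/n), and one further df is used. For example, at r = 0.5 and n = 51, SE = 0.1094 × sqrt(0.75) = 0.0947, the ratio is 0.31/0.0947 = 3.27, and power is 0.900.

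At 30% dropout, 130 × 0.7 = 91 remain, about 45 per arm.

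| r (assumed) | Variance removed | Power, 51/arm | 95% CI half-width, 51/arm | Power, 45/arm |
|---|---|---|---|---|
| 0 (unadjusted) | 0% | 0.80 | 0.217 cm | 0.75 |
| 0.3 | 9% | 0.84 | 0.207 cm | 0.79 |
| 0.5 | 25% | 0.90 | 0.188 cm | 0.86 |
| 0.7 | 49% | 0.98 | 0.155 cm | 0.96 |

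Half-widths are t quantile × SE. The table is for a difference in means, the scale on which the sample size was set.

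**3. Chance imbalance.** If the preoperative SDs match the stated ones, the baseline difference between arms also has SE 0.1094 cm at 51 per arm, and sqrt(0.61/65) = 0.0969 cm at 65 per arm.

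- P(|difference| > 0.10 cm, about a third of the margin) = 36% at 51 per arm and 30% at 65.
- P(|difference| > 0.155 cm, half the margin) = 16% and 11%.

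Given a baseline difference d, the expected shift in the unadjusted day-3 difference is r × d. With d = 0.155 and r = 0.7 that is 0.109 cm, about a third of the margin.

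**The case against.** **Efficiency, not validity.** Chance imbalance averages to zero over randomisations, and the unadjusted interval already allows for it. With 102 evaluable patients the unadjusted comparison has the claimed 80% power. This stands, and it limits the point to precision and to the accuracy of the result actually obtained.

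**The correlation is unknown.** Day-3 thickness follows surgery, and the article itself expects early quadriceps swelling, which could lower r. At r = 0.3 the gain is small (9% of variance). This stands, which is why the low value is in the table.

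**The mixed model already adjusts.** Gender, age, height and weight may explain part of the variance, so the gain over that model follows the partial correlation and is smaller than tabulated. This stands for the GLMM. The Mann-Whitney test and bootstrap interval have no adjustment at all.

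**Baseline is measured after randomisation.** This does not bar it as a covariate: it precedes surgery, and patients and evaluators are blinded.

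Two stronger readings are tempting, and the article supports neither:

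- A reader might infer that the GLMM stacks preoperative and day-3 values with a group term only. The group coefficient would then average a null preoperative contrast with the day-3 effect. A true deficit of 0.31 cm would appear as 0.155 cm and pass the margin in 32 to 37% of trials (r from 0.8 down to 0.5) instead of 2.5%. The article does not say that preoperative values enter as outcomes or that a time term is absent, and a day-3-only model fits its wording equally well. This remains hypothetical, and it would not touch the Mann-Whitney comparison.
- A reader might infer that the secondary models have the same gap. Their covariate list is open-ended, and the first-order autocorrelation across time points lets preoperative values enter as repeated measures. No defect can be claimed there.

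**Conclusion.** The point holds as a matter of precision. The primary analysis, as stated, makes no use of a baseline value the trial already collects.

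At the planned 51 per arm, adjustment would lift power modestly if r is near 0.3 and substantially from 0.5 upward. The gain matters more at 45 per arm, where the trial's own dropout figure puts the unadjusted comparison below its 80% target. Adjustment then brings power just short of the target at r = 0.3 and above it at r = 0.5.

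The omission itself is certain from the text. The size of the gain is not, because it rests on an assumed r, on equal variances before and after surgery, and on a comparison of means rather than medians. It is an upper figure relative to the covariate-adjusted GLMM. The documents do not support a claim of average bias or of an inflated false non-inferiority rate.

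**What to change.** Make the primary analysis an ANCOVA of day-3 thickness of the operated limb on group, preoperative thickness of the same limb, gender, age, height and weight. Report the adjusted group difference (tourniquet minus non-tourniquet) with its 95% CI, and conclude non-inferiority if the lower limit lies above -0.31 cm. If the residuals are clearly non-Gaussian, use a robust or bootstrap interval for the same adjusted difference. The Mann-Whitney test and difference of medians can stay as supporting results.

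If a repeated-measures model is preferred, state that it includes time and group-by-time terms and that the day-3 contrast is the one read against the margin. That sentence also rules out the pooled reading.

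**Cost.** No new patients or measurements are needed. Replacing the primary test is more than an edit, though: 84 participants had been recruited when the article was written, and the Auditing and amendments section requires major amendments to be communicated, including to the ethics committee. The change should be documented, dated and made before unblinding.
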